## Abstract

**Background:**

The prevalence of chronic constipation is about 15 % in Western countries with a significant impact on quality of life and health care costs. The first-line therapy, based on medical treatment combined with laxatives and dietary rules, is often disappointing. Interferential therapy is a new treatment that has demonstrated its efficiency in the treatment of chronic constipation in children and encouraging results in adults. The primary objective of this study is to assess the efficacy of interferential therapy during 8 weeks in adult patients. The secondary objectives are to assess this new and noninvasive therapy in terms of persistence of the clinical efficacy, colonic transit time, ano-rectal manometry, patient satisfaction and quality of life (QoL), and tolerance.

**Methods/Design:**

Design: multicenter, prospective, randomized, placebo-controlled, double blind, two-parallel groups study. Setting: nine French adult gastroenterology centers. Inclusion criteria: adult patients with a history of chronic constipation refractory to medical treatment for at least 3 months. Treatment groups: (1) interferential-experimental group (effective stimulation); (2) placebo-control group (sham stimulation). Randomization: 1:1 allocation ratio. Evaluation times: inclusion (T0, randomization), baseline assessment (T1), start of stimulation (T2), intermediary assessment (T3, 4 weeks), end of stimulation (T4, 8 weeks), follow-up (T5 and T6, 1- and 6-month). Endpoints: (1) primary: short-term efficacy at T4 (treatment response defined as three or more spontaneous, complete bowel movements per week); (2) secondary: efficacy at T5 and T6, symptoms (Patient Assessment of Constipation Symptoms questionnaire), colonic transit time, anorectal manometry, patient satisfaction (analogical visual scale), patient QoL (Patient Assessment of Constipation Quality of Life Questionnaire), side/unexpected effects. Sample size: 200 individuals to obtain 80 % power to detect a 20 % difference in treatment response at T4 between the two groups (15 % of lost to follow-up patients expected).

**Discussion:**

The randomized, double-blind, placebo-controlled design is the most appropriate to demonstrate the efficacy of a new experimental therapeutic (Evidence-Based Medicine Working Group classification). National and international recommendations could be updated based on the findings of this study.

**Trial registration:**

Current controlled trials NCT02381665 (registration date: February 13, 2015).

## Background

The prevalence of chronic constipation is about 15 % in Western countries with a significant impact on quality of life and health care costs [1]. Two subtypes of constipation can be identified: slow transit constipation (STC), characterized by impaired propulsion of stool and due to dysfunction of colonic smooth muscle (myopathy) or its innervation (neuropathy), or both; and evacuation disorders, characterized by difficulty or inability with stool expulsion. They include disorders of the anorectal function, such as dyssynergic defecation, as well as structural disorders, such as rectocele, descending perineum syndrome and rectal prolapse [2]. In case of failure, few treatment options are currently available. Surgery can sometimes be discussed for intractable chronic constipation. Indeed, sub-total colectomy can be proposed in case of STC but is associated with a significant morbidity. In case of pelvic floor disorders, a specific surgical treatment can be indicated. However, surgery is invasive and has a significant morbidity, and the results are inconsistent. Recently, some studies have assessed the efficacy of sacral neuromodulation in the treatment of chronic constipation with some success, but this technique is expensive and requires the surgical implantation of a medical device [3]. More recent works, including a randomized trial, have shown the efficacy of interferential current stimulation in the treatment of chronic transit constipation in children [4–6]. This treatment is used daily, at home, and uses four adhesive surface electrodes, two abdominal (placed below the costal margin) and two paraspinal (placed between T9 and L2), producing two sinusoidal currents crossing the body, 1 h per day for 1–3 months.

To date, only one open-label study has evaluated this technique in adults and has shown encouraging results in 3 months with an efficiency in 7/11 patients (63.6 %) in the number of stools, severity score of constipation and quality of life score associated with a significant improvement in the colonic transit time measured by radiomarkers [7]. These data are of particular interest since laxative treatments are often disappointing, are expensive and may have adverse events.

These observations prompted us to establish a multicenter, prospective, two-group, placebo-controlled, double-blind, randomized study with the primary objective of assessing the efficacy of interferential therapy during 8 weeks in adult patients with severe chronic constipation. The secondary objectives are to assess this new noninvasive therapy in terms of persistence of the efficacy, colonic transit time, ano-rectal manometry, patient satisfaction and quality of life (QoL), and tolerance.

## Methods/Design

### Design

This multicenter, prospective, randomized, placebo-controlled, double-blind, two-parallel group study is performed to assess the efficacy of the use of interferential therapy: the experimental group (effective stimulation) and control group (sham stimulation). The study protocol was designed using the recommendations of the Consolidated Standards of Reporting Trials (CONSORT) statement.

### Participants

The details of the inclusion and exclusion criteria are provided in ‘List of selection criteria’. The main inclusion criteria are adult patients with a history of medical therapy-refractory chronic constipation for more than 6 months, defined as two or fewer spontaneous, complete bowel movements per week for a minimum of 6 months or as a sensation of incomplete evacuation or straining during defecation. The main exclusion criteria are patients with constipation secondary to anorectal malformations, to colorectal or anal organic lesions or to a pelvic floor disorder, to a drug, to neurologic, endocrine or metabolic disorders.

**List of selection criteria**

Inclusion criteriaAdults patients (≥18 years of age) of either sexSubjects with a history of chronic constipation defined as: two or fewer spontaneous, complete bowel movements per week for a minimum of 6 months before the screening visit or as a sensation of incomplete evacuation or straining during defecation with at least 25 % bowel movementsSubjects with chronic constipation lasting for more than 6 monthsSubjects with chronic constipation refractory to medical treatment for at least 3 months (failure or intolerance of medical treatment)Subjects have to interrupt any laxative treatment but during the study, patients are allowed, in case of absence of bowel movements for 3 or more consecutive days, to take up 15 mg of bisacodyl (Dulcolax, Boerhinger Ingelheim) as rescue medicationSubjects affiliated to or beneficiary of a social security systemSubjects who have signed written informed consent

Exclusion criteriaMinors or pregnant or breast-feeding womenSubjects with chronic constipation secondary to anorectal malformations, to colorectal or anal organic lesions or to a pelvic floor disorder considered by the investigator as necessitating a surgical treatment (rectal prolapse exteriorized, rectocele, enterocele)Subjects with current implanted cardiac pacemakers, defibrillators, cardiac pumps, spinal stimulators or other implanted electronic devicesSubjects with chronic constipation secondary to a drug, to neurologic, endocrine or metabolic disordersSubjects with a history of partial colectomySubjects with megacolon, megarectum, colonic inertiaSubjects with skin lesions preventing the installation of the electrodesWomen without effective contraception (hormonal or intrauterine device)Subjects misunderstanding the written and spoken French languageSubjects participating in another biomedical research protocol

### Treatments

The device procedure (effective or sham) will be blinded; neither the patient nor the physician responsible for the prescription will be informed of the nature of the device. Whatever the group (control or experimental), the patients will follow the same procedure, will receive a device looking exactly the same and will have the same follow-up. This design has already been used in randomized studies using electrical stimulation [4, 8]. The practitioner that will give the instructions concerning the use of the device will be aware of the sham or effective stimulation since he/she will need to give different instructions according to the device (sham or effective). The feasibility of this treatment has previously been demonstrated [7].

#### Interferential-experimental group: effective stimulation

The patients will receive stimulation 1 h per day every day at home during 8 weeks. There is no “dose adjustment;” if the stimulation is not well tolerated, it will be stopped according to the opinion of the practitioner. The stopping criteria are as follows: severe pain or neurological symptoms (paresthesia, burning, shaking). Unblinding of treatment could be done by contacting the coordinating investigator.

#### Placebo-control group: sham stimulation

The patients will receive the sham device without any stimulation 1 h per day every day at home for 8 weeks. The device will be the same as the one used in the experimental group but there will not be any stimulation. The device will not be active in this group; thus, no side effects or intolerance is expected. However, if any side effects are reported (e.g., pain), the stimulation will be stopped in accordance with the cessation criteria detailed below. Unblinding of treatment could be made as described above.

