In the current study, patients receiving the sham device will not feel any stimulation, and they will use the device during a total time of 1 h for 8 weeks. The sham device will be programmed in this way, and its external aspect will not differ from the effective device. Patients with the effective stimulation will feel the stimulation during the whole stimulation period (1 h for 8 weeks). However, since the instructions need to differ between the two patient groups, the practitioner that will give the instructions must absolutely differ from the one who will follow the patients. All patients will be told that they may or may not feel something with the stimulation because people always respond differently to the stimulation. Because only one practitioner will know which device is attributed to the patient, participants will be instructed not to reveal or discuss the type of treatment characteristics they are experiencing with the other practitioner. The other option would have been to use a sham stimulator inducing a short (few seconds or minutes) stimulation before stopping. Our choice is supported by two main reasons: The first reason is to be in accordance with the literature. Indeed, a recent review of the literature on randomized controlled trials about transcutaneous electric nerve stimulation showed that the majority of the studies reported using an inactive device looking identical in appearance to the active one [14]. The second reason is supported by the physiological effect of somato-sympathetic reflexes. Indeed, some studies have demonstrated that stimulating the skin could induce somato-visceral reflexes that can modify visceral functions. Since these activities can be induced by a very short stimulation, it seems that, to be a real control, a sham stimulator should not induce any stimulation [15–17].

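### The rule for stopping stimulation is worded differently in the two arms and points to criteria that do not follow; it needs one wording usable without knowing the allocation

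*Protocol article*

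**What the plan says.** Three places in the protocol article bear on when stimulation is stopped.

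- **Treatments (introduction).** "Whatever the group (control or experimental), the patients will follow the same procedure". The same paragraph sets the blinding: "neither the patient nor the physician responsible for the prescription will be informed of the nature of the device". It also creates one unblinded role: "The practitioner that will give the instructions concerning the use of the device will be aware of the sham or effective stimulation". The Discussion adds that "the practitioner that will give the instructions must absolutely differ from the one who will follow the patients".
- **Interferential-experimental group.** "if the stimulation is not well tolerated, it will be stopped according to the opinion of the practitioner", followed by "The stopping criteria are as follows: severe pain or neurological symptoms (paresthesia, burning, shaking").
- **Placebo-control group.** The device is inactive, so "no side effects or intolerance is expected"; but "if any side effects are reported (e.g., pain), the stimulation will be stopped in accordance with the cessation criteria detailed below".

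No section after the sham paragraph, from concomitant medications to the abbreviations, contains a stopping criterion. The nearest text is the tolerance item under Secondary endpoints, which lists events to be analysed and is not a rule for stopping.

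**The concern.** The active-arm paragraph qualifies pain as severe. The sham paragraph speaks of any side effect and gives pain, unqualified, as its example. A site holding only this text cannot tell whether a sham patient with mild or moderate pain is to be stopped, or whether the answer would be the same for an active patient.

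In a double-blind trial, a stopping rule that depends on the arm is a problem whoever applies it. If the blinded follow-up physician decides, the physician must know the allocation to choose the rule. If the unblinded practitioner decides, the decision is made with knowledge of the arm. Neither arm paragraph says which of the two it is.

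At stake are the blind and the comparability of treatment stops. The primary endpoint could also be touched, because response is defined over the 8 weeks of treatment.

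**Working it through.** **Step 1: the passages side by side.**

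| | Active arm | Sham arm |
|---|---|---|
| Trigger | Severe pain or neurological symptoms; also poor tolerance | Any reported side effect, pain as example |
| Criteria cited | Stated on the spot | Said to follow; none do |
| Who decides | The practitioner, not specified further | Not stated |
| Treatments introduction | Same procedure as sham | Same procedure as active |

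**Step 2: two readings of the sham sentence.**

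- *Literal.* Any side effect leads to stopping. The rule then differs by arm and contradicts the Treatments introduction.
- *Common rule.* The reference to cessation criteria means those in the active-arm paragraph, and the pointer should look back, not forward. The rule is then the same in both arms, but the trigger wording and the pointer are wrong.

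The text does not settle which is meant. Later in the same sham paragraph, unblinding is correctly referred back to the text above, so a site cannot simply assume that the forward pointer is a slip.

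**Step 3: how much could it matter for the primary endpoint?** The plan gives no stopping rate, so there is no planned figure to reproduce. Inputs from Sample size, power and statistical methods: 15% response in the control group and a 20-point difference, hence 35% in the active group. Assumptions: stopped patients count as non-responders, stopping is unrelated to what the response would have been, and the stopping rates are purely illustrative.

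Formula: observed response = planned response × (1 − proportion stopped).

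| Sham stopped | Active stopped | Sham response | Active response | Difference (points) |
|---|---|---|---|---|
| 0% | 0% | 15.00% | 35.00% | 20.00 |
| 5% | 5% | 14.25% | 33.25% | 19.00 |
| 10% | 5% | 13.50% | 33.25% | 19.75 |
| 5% | 10% | 14.25% | 31.50% | 17.25 |
| 15% | 5% | 12.75% | 33.25% | 20.50 |
| 5% | 0% | 14.25% | 35.00% | 20.75 |
| 15% | 0% | 12.75% | 35.00% | 22.25 |

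The last two rows take the literal reading to its extreme, with stops in sham only. The shift is 0.15 × 0.05 = 0.75 points to 0.15 × 0.15 = 2.25 points. It would be the same if the device had no effect and both arms responded at 15%.

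With 85 evaluable per arm (100 × 0.85), the power of the two-sided 5% test is 0.86 with no stopping. In the next four rows it is 0.84, 0.87, 0.77 and 0.90. The low value arises when more active than sham patients stop, which is not the direction that the literal wording suggests. Values above 0.86 come from a distorted comparison and are no gain.

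**The case against.** The best defence is the common-rule reading. The sham sentence does not stop at any side effect; it adds that stopping follows the cessation criteria, and the article prints only one set. That fits the promise of a single procedure. The pointer may also be left over from the full protocol, which is not at hand. This stands as far as it goes: different thresholds are a possible reading and not an established fact. It does not remove the conflict between the printed statements.

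A reader might infer more than the text supports:

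- **That blinded staff cannot apply the rule at all.** The plan provides an unblinded practitioner who could. The gap is that the deciding role is not named; the Discussion uses the word practitioner for both roles.
- **That no active patient with milder pain would be stopped.** The poor-tolerance clause allows it, on the practitioner's opinion.
- **That the active device would look better tolerated.** Tolerance is analysed from side effects, not from discontinuations. A sham patient stopped for a side effect already counts as having one.
- **That stops drain the analysis or the 15% allowance for loss to follow-up.** Stopping the device is not leaving follow-up. The full analysis population keeps randomized patients evaluated at T2, and a stop that the protocol itself requires is not obviously a major deviation for the per-protocol set.

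**Conclusion.** The concern holds as an inconsistency in an operative rule. The Treatments introduction and the two arm paragraphs disagree on when stimulation stops, one of them cites criteria that are not there, and the deciding role is open. If the sham sentence is followed literally, the blind is put at risk and stops might not be comparable between arms. That they will not be comparable is not shown, since it depends on the literal reading and on rates that the documents do not give.

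The likely effect on the primary endpoint is small: 0.75 to 2.25 points on a planned difference of 20, even if 5% to 15% of sham and no active patients were stopped, under the assumptions stated. The case rests on blinding and consistent conduct across sites, and much less on power. It should be corrected, but it does not threaten the primary analysis.

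**What to change.** - Reconcile the Treatments introduction and the two arm paragraphs into one stopping rule in a common section, identically worded for both arms and applicable without knowledge of the allocation. What the rule says is for the sponsor's clinicians to decide; no threshold is proposed here.
- Correct the cross-reference in the sham paragraph so that it leads to that rule.
- State which practitioner decides on stopping, in terms that separate the instructing role from the follow-up role.
- Record the reason for each stop in the same categories in both arms.

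The cost is protocol wording, the clinicians' confirmation of one rule and, if not already present, one field on the case report form. The article gives the trial status at submission as not yet recruiting, which is when the change is cheapest. Sample size and analysis are unaffected.

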#### Concomitant permitted and prohibited medications

In case of absence of bowel movements for 3 or more consecutive days, the patients are allowed to take up 15 mg of Bisacodyl (Dulcolax, Boerhinger Ingelheim) as rescue medication because it is simple to use and has satisfactory tolerance and rapid action [9]. All other laxative drugs are forbidden during the study.

#### Medical device

The interferential therapy device uses a 6-V battery-operated interferential stimulating machine (Flexitim IF Tenscare, Fuji Dynamics, Hong Kong, CE mark 0473, Market authorization December 2009). The device is marketed in France by A-Legrand Co. (http://www.a-legrand.com). Interferential treatment delivers a 4-kHz carrier frequency, a beat frequency of 80–160 Hz and an intensity of less than 33 mA. The stimulation will be done according to the procedure described by Ismail et al. [6]. This technique uses four adhesive surface electrodes, two abdominal (placed below the costal margin) and two paraspinal (placed between T9 and L2), producing two sinusoidal currents crossing the body. To ensure the proper placement of the electrodes, the first stimulation must be made in the presence of the practitioner. During the 8-week treatment period, the stimulation protocol is home-based and self-applied by the patient for 1 h per day every day.

### Recruitment and follow-up

#### Screening and inclusion

During a 2-week observational period, the eligible patients will be asked to report the number of spontaneous, complete bowel movements per week to the physicians (partners of the study) in a bowel diary (T0). The patients who meet all the inclusion and exclusion criteria will be randomized into one of the two treatment groups after completing the consent form and getting it to the investigator.

#### Randomization

Computer-generated randomized lists will be drawn up before the beginning of the study, using a permuted block design, under the responsibility of the clinical research unit (AP-HM). The randomization will be stratified by center (1:1 allocation ratio). The allocation sequences will be sequentially numbered. The pharmacist responsible for the medical device distribution in the participating centers will take care of the lists. Prior to the study period, the participant, the treating medical staff and the investigators will all be unaware of the allocation.

#### Follow-up and data collection

The evaluation will be performed at six different time points: baseline (T1), initial visit (T2, beginning of the stimulation), intermediary visit (T3, 4 weeks after T2), end of stimulation (T4, 8 weeks after T2), and 1 and 6 months after the end of stimulation (T5 and T6). Minimal data of lost to follow-up patients will be collected to determine whether they differ from the others. The study procedure and data collection are detailed in Table 2.

**Table 2 Tab2:** Study procedure

	T0	T1	T2	T3	T4	T5 and T6
Consent	x					
Randomization	x					
Clinical examination	x	x	x	x	x	x
Colonic transit		x			x	
Ano-rectal manometry		x			x	
Stimulation						
Constipation symptoms (diary, PAC-SYM)		x	x	x	x	x
Quality of life (PAC-QOL)		x	x	x	x	x

*T0* pre-inclusion, *T1* baseline assessment (T0 ± 15 days), *T2* beginning of stimulation (T1 ± 15 days), *T3* intermediary assessment (T0 ± 4 weeks), *T4* end of stimulation (T0 ± 8 weeks), *T5* follow-up at 1 month, *T6* follow-up at 6 months and end of study

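### The Table 2 footnote times T3 and T4 from T0 (pre-inclusion), while the text of the same section times them from T2, the start of stimulation

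*Protocol article*

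**What the plan says.** Under Follow-up and data collection, the protocol article's text lists the evaluation times. The intermediate assessment is the "intermediary visit (T3, 4 weeks after T2" and the last on-treatment assessment is the "end of stimulation (T4, 8 weeks after T2". T2 is the visit at which stimulation begins. T5 and T6 follow 1 and 6 months after stimulation ends.

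The text then refers the reader on: "The study procedure and data collection are detailed in Table 2". The footnote to that table defines the visits again. T0 is pre-inclusion. The next two entries are "baseline assessment (T0 ± 15 days" for T1 and "beginning of stimulation (T1 ± 15 days" for T2. T3 is "intermediary assessment (T0 ± 4 weeks" and T4 is "end of stimulation (T0 ± 8 weeks".

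The treatment section fixes the duration of exposure: "The patients will receive stimulation 1 h per day every day at home during 8 weeks". The sham arm and the Medical device section give the same 8 weeks. The Primary endpoint section places response at the end of those 8 weeks of stimulation.

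**The concern.** One section gives the same two visits two different starting points. T0 and T2 are separate columns in Table 2. Consent and randomization belong to T0, baseline colonic transit and manometry to T1, and stimulation starts at T2. Unless all three fall on one day, counting 8 weeks from T0 does not reach the end of 8 weeks of stimulation, so the footnote's date for T4 conflicts with its own label for that visit.

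T4 is the visit for the primary endpoint. It is also the only time after baseline at which colonic transit and manometry are repeated. Nine centers take part, and a schedule table with its footnote is what a site is likely to work from when booking visits. A site that did so would see the patient before the planned course was complete. If it also took that visit as the end of stimulation, the 1- and 6-month follow-up visits would move earlier with it.

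**Working it through.** No sample size or power figure bears on this point. The check is day arithmetic on the footnote's own entries.

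**Inputs** (all from Follow-up and data collection, except the last two)
- Text: T3 = T2 + 28 days; T4 = T2 + 56 days.
- Footnote, with ± read as +: T3 = T0 + 28 days; T4 = T0 + 56 days.
- Footnote, with ± read as +: T1 is 0 to 15 days after T0, and T2 is 0 to 15 days after T1.
- Treatments: 8 weeks of daily stimulation from T2, which is 56 days.
- Secondary endpoints: the transit test takes 6 days of markers and a film on day 7.

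**Why ± is read as +.** Taken literally, the footnote would allow the end of stimulation to come 8 weeks before pre-inclusion. Stimulation cannot precede T0, because Table 2 places consent and randomization there. Even as a window, the latest date that the footnote allows for T4 is T0 + 56 days, which is the date used here. T0 is treated as a single day.

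**Formula.** Let g = T2 − T0, so g runs from 0 to 15 + 15 = 30 days. The footnote's T4 is T0 + 56 = T2 + (56 − g). The text's T4 is T2 + 56. The difference is −g. T3 shifts by the same −g, to T2 + (28 − g).

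| Gap g (days) | Footnote T3, days after T2 (28 − g) | Footnote T4, days after T2 (56 − g) | Footnote T4 early by | Text T4, days after T0 (56 + g) |
|---|---|---|---|---|
| 0 | 28 | 56 | 0 | 56 |
| 7 | 21 | 49 | 7 | 63 |
| 15 | 13 | 41 | 15 | 71 |
| 30 | −2 | 26 | 30 | 86 |

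**Which rows are plausible.** The first row needs T0, T1 and T2 on one day. If the baseline transit test is finished before stimulation starts, as a baseline measure should be, g is about a week or more, so the second row is close to a practical minimum. The last row needs both 15-day intervals used in full. It also puts T3 two days before stimulation begins.

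**Later visits.** The text counts T5 and T6 from the end of stimulation. If stimulation runs on to day 56 whatever the date of T4, they stay where they are. If a site stops at the footnote's T4, they come g days early.

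**The case against.** The strongest reply is that the slip corrects itself. The footnote labels T2 as the beginning of stimulation and T4 as its end, the treatment sections fix 8 weeks of daily use, and the text just above the table gives the right anchor. The printed ± cannot be followed literally, so a site would have to interpret the entry anyway and would probably choose T2. In the 30-day case the schedule fails visibly at T3, before T4 is reached. All of this stands, and it keeps the point minor. It does not remove the conflict, because the text sends the reader to Table 2 for the detail and no plausible reading of the T4 entry there gives T2 + 8 weeks once T2 is later than T0.

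A second reply concerns the endpoint. Response is defined over the 8 weeks, with bowel movements recorded in a diary, and not as a measurement on the visit day. An early T4 would leave the diary period incomplete, and a site might notice. This stands too. A reader might infer that an early T4 would dilute the contrast between active and sham. The documents do not show that response would be classified on a shortened period, so that inference is not made here.

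The rest of the article should not be read as unanimous for T2 either. The abstract gives 4 and 8 weeks without naming an anchor. The Primary endpoint section uses stimulation as the reference in one sentence and the trial in another. The treatment sections fix how long the device is used, not when visits occur.

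**Conclusion.** The contradiction is real and can be checked within one section. Severity is minor and confidence is high. It is probably a drafting slip, with T0 printed for T2 and ± for +. It matters because it lies in the visit schedule and concerns the primary-endpoint visit.

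Its size depends on reading ± as + and on the T0–T2 gap. The footnote's T4 is early by that gap, for example 15 days early with 41 of 56 stimulation days done. T5 and T6 would move only if a site took the early visit as the end of stimulation.

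Two stronger readings are not supported. One is that response would be judged after less than half of the course: the 26-day figure is the extreme of two stacked intervals, not an expected schedule. The other is that the comparison would be biased: both arms follow the same schedule, and nothing in the article suggests that the footnote would be applied differently by arm.

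**What to change.** In the Table 2 footnote, change the T3 entry to T2 + 4 weeks and the T4 entry to T2 + 8 weeks, to match the text of the section. If + was meant in the T1 and T2 entries, replace ± with + there as well. If a visit window was meant, state the target day and the window separately.

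The cost is two corrected entries and possibly two changed symbols. No visit is added or moved from the schedule in the text, and the sample size, endpoint definition and analysis do not change. The Primary endpoint section needs no rewording for this point.
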